**Design:**

This is a multi-center pragmatic randomized clinical trial to investigate whether early AED withdrawal improves cognitive function, in terms of attention, executive function and intelligence, quality of life and behavior, and to confirm safety in terms of eventual seizure freedom, seizure recurrences and “seizure and AED freedom.” Patients will be randomly allocated in parallel groups (1:1) to either early or late AED withdrawal. Randomization will be concealed and stratified for preoperative IQ and medical center. In the early withdrawal arm reduction of AEDs will start 4 months after surgery, while in the late withdrawal arm reduction starts 12 months after surgery, with intended complete cessation of drugs after 12 and 20 months respectively. Cognitive outcome measurements will be performed preoperatively, and at 1 and 2 years following surgery, and consist of assessment of attention and executive functioning using the EpiTrack Junior test and intelligence expressed as IQ (Wechsler Intelligence Scales). Seizure outcomes will be assessed at 24 months after surgery, and at 20 months following start of AED reduction. We aim to randomize 180 patients who underwent anticipated curative epilepsy surgery below 16 years of age, were able to perform the EpiTrack Junior test preoperatively, and have no predictors of poor postoperative seizure prognosis (multifocal magnetic resonance imaging (MRI) abnormalities, incomplete resection of the lesion, epileptic postoperative electroencephalogram (EEG) abnormalities, or more than three AEDs at the time of surgery).

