## Background

For children with refractory epilepsy, epilepsy surgery is a successful and widely accepted therapeutic option with postoperative seizure freedom rates ranging from 41 to 93 % [1, 2]. In patients who have been operated on and who have reached seizure freedom the ultimate goal is to discontinue antiepileptic drug (AED) use and to improve developmental capacities [3–5]. AEDs are known to have cognitive side-effects, particularly in children. Most affected cognitive functions are attention, vigilance and psychomotor speed [6–9]. AED reduction has been reported to improve cognitive processing under time pressure [8, 10], psychomotor speed and alertness [11–13], processing speed [14], verbal memory [15] and Intelligence Quotient (IQ) [9]. The growing body of evidence that cognitive functioning improves after AED withdrawal has increased awareness of the possible benefits of the earliest possible withdrawal of AEDs after epilepsy surgery. Two recently published studies [16, 17] showed that early withdrawal of drug treatment unmasks incomplete surgical success and AED dependency sooner, but not at the cost of worse long-term seizure outcome. Thus, early AED withdrawal would discern the few that require further AEDs from the many that can safely stop, without changing the chance of regaining seizure freedom. A pressing question is whether early AED withdrawal improves cognitive outcome measures, as compared to current care with usually later AED withdrawal. To answer that question we designed a pragmatic randomized clinical trial to investigate the benefits and safety of early AED withdrawal after epilepsy surgery in children. We hypothesize that 1) children who discontinue AED’s early have better cognitive scores, behavior and quality of life than those who discontinue late, particularly at 1 year after surgery (when 1 group is without AEDs and the other is still on AEDs), and maybe persisting from then on, and 2) early AED withdrawal is safe and does not cause more recurrences that are unresponsive to restart of medication, than late withdrawal.

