#### Outcome parameters

Cognitive outcome: differences in EpiTrack scores, IQ scores and other continuous outcome measures of neuropsychological assessment will be analyzed using independent samples *t*-tests or other tests depending on distributions. EpiTrack and IQ differences will be assessed cross-sectionally to answer the primary research question. Additionally, longitudinal changes in EpiTrack measures and IQ compared to preoperatively will be assessed between both treatment arms using linear mixed models. We will calculate a number needed to treat, expressed as the number of patients required to taper drugs earlier to achieve one more patient with improvement in attention. Analyses will be considered statistically significant if 95 % confidence intervals for group differences do not include 0, compatible with a 2-sided *p* < 0.05. For chances of eventual seizure freedom and “seizure and AED freedom”; we will calculate a relative risk and a risk difference with 95 % confidence intervals. Chances of eventual seizure freedom and “seizure and AED freedom” will be compared between the groups at 24 months after surgery and at 20 months following start of AED withdrawal; for the early withdrawal arm this will be at 24 months and for the late withdrawal arm at 32 months.

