With regard to safety; due to the design of the trial, an interim safety analysis comparing both treatment arms at one moment is not possible. This is because we expect in both arms relapse risks to increase particularly once AED withdrawal is started. Thus, in the early withdrawal group recurrences probably occur sooner than in the late withdrawal group, although the total risk of relapse at the end of follow-up is not expected to differ between groups. This implies that at interim time points, when inherently more patients are under AED reduction (at increased risk of relapse) in the early arm, a fair comparison of relapse between both groups is not feasible. To deal with this, we will assess safety in each arm separately. The study intervention will be considered safe when seizure recurrences occur in less than 40 % of both treatment arms. This percentage is chosen based on the general seizure freedom rate after childhood epilepsy surgery of 41 to 93 % [1, 2]. Based on previous identification of risk factors for seizure recurrences, we expect recurrence rates in the patients included in the trial to be < 30 %, due to exclusion of patients with identified risk factors [1, 16, 22, 23]. We do not expect, however, the seizure status to be better than in normal clinical practice. Because of the expected cognitive benefit due to a longer AED-free period, a 40 % rate of seizure relapse will still be accepted. The DSMB statistician will analyze the number of patients with seizure recurrences every 3 months during trial duration, in order to allow early awareness of unexpected high numbers of recurrences, exceeding the 40 % limit. In this sequential testing safety model (Fig. 2), a 1-sided *p* value < 0.05 will be considered significant for the safety monitoring [24, 25].

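### The seizure-freedom comparison meant to confirm safety has no margin, and at 75 to 90 patients per arm a non-significant difference cannot confirm it

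*Protocol article*

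**What the plan says.** The Design paragraph of the abstract gives the safety aim as "to confirm safety in terms of eventual seizure freedom, seizure recurrences". The second hypothesis in the Background is that "early AED withdrawal is safe and does not cause more recurrences that are unresponsive to restart of medication, than late withdrawal". The Discussion repeats the safety hypothesis for relapse rates and eventual seizure outcomes. Study objectives lists these outcomes as secondary.

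Under Outcome parameters, the plan for seizure freedom, and for combined seizure and drug freedom, is: "we will calculate a relative risk and a risk difference with 95 % confidence intervals". These outcomes "will be compared between the groups at 24 months after surgery and at 20 months following start of AED withdrawal". The one criterion given in that section, placed after the cognitive analyses and before the seizure sentences, is: "Analyses will be considered statistically significant if 95 % confidence intervals for group differences do not include 0".

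The Sample size calculation rests on EpiTrack Junior only. It gives no margin, acceptable loss or power for seizure freedom.

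Safety monitoring adds a numerical rule of its own: "The study intervention will be considered safe when seizure recurrences occur in less than 40 % of both treatment arms". Each arm is assessed separately.

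**The concern.** Confirming that early withdrawal is no worse requires the data to exclude a loss large enough to matter. A test of difference does not do this: a small trial often returns a non-significant difference even when a real loss exists. Without a stated margin, nothing in the plan separates a result that supports safety from one that is merely imprecise.

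The Discussion gives the need for firm proof of safety as part of the case for randomizing, so the final seizure result is likely to inform practice. The article has already read a non-significant result as no association once: under Safety monitoring, a retrospective hazard ratio for recurrence of 0.94 (CI 0.86–1.02 per 3 months) leads to an expectation of comparable recurrence in both arms. The trial's own seizure comparison could be read the same way.

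**Working it through.** **Inputs from the article.** At least 75 patients per arm; 180 in total as the target, so 90 per arm; 1:1 allocation; two-sided 95% intervals; expected recurrence below 30%; safety limit 40%.

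**Assumptions.** The article gives no rate for eventual seizure freedom. I use 70% in the late arm (the complement of 30% recurrence), and also 80% and 90%, because children who relapse may regain control. The 10-point loss is illustrative. It equals the gap between 30% and 40% in the recurrence rule, which concerns a different endpoint.

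**1. The plan's own sample size.** n per arm = 2 × (1.96 + 0.84)² × 4.70² / 2.16² ≈ 74.3, so 75. Power at 75 is 80.4% by the normal formula and 79.8% by the noncentral t. The stated figure is reproduced, but it concerns EpiTrack Junior.

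**2. Chance that a true 10-point loss is non-significant.** Power = Φ[(0.10 − 1.96 × SE0) / SE1], where SE0 uses the pooled rate and SE1 the separate rates.

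For 70% v 60% with 75 per arm:
- SE0 = √(2 × 0.65 × 0.35 / 75) = 0.0779
- SE1 = √((0.21 + 0.24) / 75) = 0.0775
- Power = Φ(−0.68) = 24.8%, so the loss is missed 75.2% of the time.

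| Late v early | Missed, 75 per arm | Missed, 90 per arm |
|---|---|---|
| 70% v 60% | 75.2% | 71.1% |
| 80% v 70% | 70.9% | 66.0% |
| 90% v 80% | 59.8% | 53.3% |

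Exact enumeration of the unpooled interval at 70% v 60% gives 74.2% and 70.3%, so the choice of formula matters little.

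**3. Expected precision with equal arms.** Half-width = 1.96 × √(2p(1 − p)/n).

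| Rate in both arms | 75 per arm | 90 per arm |
|---|---|---|
| 70% | 14.7 points | 13.4 points |
| 80% | 12.8 points | 11.7 points |
| 90% | 9.6 points | 8.8 points |

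At 70% or 80%, even an observed difference of exactly 0 would not exclude a 10-point loss. At 90% it just would.

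**4. A result that is non-significant but compatible with large harm.** Suppose 70% v 55% is observed with 75 per arm. Then SE = √((0.21 + 0.2475)/75) = 0.0781 and 1.96 × SE = 15.3 points. The interval for early minus late runs from about −30.3 to +0.3 points. It includes 0, yet it reaches a 30-point loss.

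**5. What a margin could achieve at this size.** With truly equal arms, the chance that the lower limit clears −10 points is Φ(0.10/SE − 1.96). The margin supported with 80% power is (1.96 + 0.84) × SE.

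| Rate in both arms | Chance of clearing −10 points (75 / 90 per arm) | Margin supported with 80% power (75 / 90 per arm) | n per arm for 80% power at 10 points |
|---|---|---|---|
| 70% | 27% / 31% | 21 / 19 points | 330 |
| 80% | 33% / 39% | 18 / 17 points | 252 |
| 90% | 53% / 61% | 14 / 13 points | 142 |

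**6. Whether the 40% rule fills the gap.** It does not. Recurrence rates of 15% and 38% are both under 40% although they differ by 23 points, and the rule does not address eventual seizure freedom.

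**The case against.** The significance sentence belongs to text that opens with the cognitive outcomes, and exclusion of 0 cannot apply to a relative risk, whose null value is 1. The seizure sentences can fairly be read as estimation only. This stands as a caution against saying that the seizure comparison is judged by the exclude-0 rule. It does not rescue the plan: on that reading the comparison has no criterion, while the aim is still to confirm safety.

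A reader might infer that the plan declares early withdrawal safe whenever the interval includes 0. No section says so. It is a foreseeable misreading of an aim paired with a test of difference, not a written rule.

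The article does define safety numerically through the 40% recurrence limit, with sequential monitoring, and recurrence is one of the named safety terms. That stands, but the rule works arm by arm on another endpoint.

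Seizure outcomes are secondary, and low power on a secondary outcome is not an error in itself. That also stands, and it lowers the weight of the point. Interpretive detail may sit in documents not shown, but a margin that decides whether a stated aim is met is a design choice.

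Finally, 70% is the least favourable of the three rates, and recurrence is not the complement of eventual seizure freedom when medication may be restarted. Hence the range shown.

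**Conclusion.** The point holds in this form: the article aims to confirm safety on eventual seizure freedom but states no margin for the between-arm comparison, so its stated analysis cannot deliver that conclusion. A 10-point loss would be non-significant in roughly 53% to 75% of trials, depending on the assumed late-arm rate (90% down to 70%) and on 75 or 90 per arm. With equal arms at 70%, the interval extends about 13 to 15 points either side.

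Two stronger readings are not supported. The 10 points are not the protocol's own margin for this outcome, because they are borrowed from the recurrence rule. Nor can the comparison speak to permanent loss of seizure control, since follow-up for it ends at 24 or 32 months after surgery.

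This should be fixed. It is not critical, because the outcome is secondary and the remedy is wording.

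**What to change.** Under Outcome parameters:

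- State that an interval for the seizure-freedom difference that includes 0 is not evidence of safety.
- State that safety on eventual seizure freedom will be claimed only if the lower 95% limit of the risk difference (early minus late) lies above a margin fixed in advance. The value is a clinical judgement for the trial team; 10 points is not required.
- Otherwise, report the largest loss that the interval does not exclude and make no safety claim.
- Say whether the existing significance sentence applies to the seizure outcomes.

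If the expected precision cannot support a margin the team finds acceptable, reword the aim in the Design paragraph from confirming safety to estimating the difference in seizure outcome. Give the expected half-width with its assumed rate (about 13 to 15 points at 70%). Keep the per-arm 40% limit as a separate monitoring rule.

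The change needs no extra patients or data and leaves the risk difference and its interval as planned. The cost is a more modest safety claim.

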The trial’s primary outcome measure at 1 year after surgery is cognitive functioning, in terms of attention and executive functioning, which will be assessed using the EpiTrack Junior [20]. As secondary cognitive outcome measure, intelligence will be tested with the Wechsler Preschool and Primary Scales, the Wechsler Intelligence Scale for children, or the Wechsler Adult Intelligence scale, depending on the children’s age and capabilities; scores derived are Verbal (VIQ), Performal (PIQ) and Full-scale IQ, perceptual organization or reasoning and information processing speed index scores. We will measure baseline neuropsychological status maximum 3 months before surgery (t1), and thereafter at 12 months (±2 months) (t2) and 24 months (±2 months) (t3) postoperatively. Patients and/or parents will at all neuropsychological test points complete three types of questionnaires to assess the secondary outcome measures: the Child Behavior Checklist (CBCL) and the the Hague Side Effects Scale (HASES) [21] will be completed by the parents, and the Pediatric Quality of Life Inventory^TM^ (PedsQL™) will be completed by both parents and patients. This design will allow us to assess whether cognitive performance is better in the early AED-withdrawal group, with patients being AED-free at 1 year following surgery, compared to the group that is still on full medication at the first postoperative time point. It will also enable the study of differences at a later follow-up time point, when both groups have completely discontinued medication (t3) (Fig. 1). Seizure outcome will be assessed at the moment of randomization, as seizure freedom is an inclusion criterion, at 24 months after surgery, and at 20 months following start of AED withdrawal. This design allows us to assess differences in seizure outcome at equal AED-free intervals for both groups, and at 2 years after surgery irrespective of length of AED freedom.

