### Sample size calculation

The study is powered based on the primary neuropsychological measures attention and executive function, determined with the EpiTrack Junior. We plan to study a continuous response variable from a late withdrawal (control) versus an early withdrawal (experimental) group with one control per experimental subject. For the sample size calculation, we used the reference values given in the Introduction and first validation of EpiTrack Junior [20], which presents reference values of healthy children and children with epilepsy. The mean (SD) EpiTrack Junior score in healthy children was 32.6 (2.40). In children with epilepsy the mean (SD) score was 29.5 (4.70). For sample size calculations, we calculated the sample size using the SD of the epilepsy patients. Based on numbers of patients operated on per year in the participating medical centers and excluding patients with incompletely resected lesions, multifocal MRI abnormalities, an epileptic EEG postoperatively and use of a maximum of three AEDs at time of surgery (the numbers derived from the previous retrospective study [16]), we estimated to expect to include at least 90 patients per year. By including at least 150 patients in the trial, with 75 patients per arm, we will be able to detect a true difference in the mean response of 2.16 points in EpiTrack Junior score (which corresponds to a difference of 0.46 SD) with a 2-sided alpha = 0.05 and power (1-beta) = 0.8. This difference is considered clinically relevant, as for the EpiTrack a 0.5 SD difference, can reflect a shift towards a milder impaired group of epilepsy patients [20]. One interim analysis according to O’Brien Fleming is planned after half of the planned number of patients has reached their endpoints. For reasons of possible dropout, we will aim to include 180 patients.

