### Safety monitoring

To minimize the risk for the participants in the proposed trial, we will exclude patients with those characteristics that have previously been shown to predict unfavorable outcome [16]. In our retrospective cohort we simulated the prospective randomized trial on 478 patients who would be eligible based on their exact inclusion and exclusion criteria. In this group, the interval to start of AED reduction was not associated with seizure recurrences during or after AED withdrawal (*p* = 0.155, HR 0.94; CI 0.86–1.02 per 3 months), nor with eventual seizure freedom (*p* = 0.551, HR 0.96; CI 0.85–1.09) or seizure and AED freedom (*p* = 0.516, HR 1.01 CI 0.97–1.06, Cox regression analysis). Based on these analyses, we expect an overall comparable percentage of seizure recurrences in both treatments arms, similar to the number or recurrences encountered in everyday clinical practice when starting tapering of AEDs.

We appointed a Data Safety Monitoring Board (DSMB) that will analyze our data to warrant safety and to monitor inclusion rates and assess inclusion feasibility. At 24 months a blinded interim-analysis will be performed by the DSMB to investigate superiority of one of the treatment arms with regard to the primary outcome measure. If the difference in attention between groups is more than 1 SD (age appropriate average reaction time), the DSMB may advise to prematurely stop the trial, if early withdrawal shows to be superior, the remaining patients in the late withdrawal group who still await start of AED reduction are allowed to withdraw medication from that time on. A test result with a 2-sided *p* < 0.0054 will be declared significant.

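### The final primary test is left at two-sided 0.05 after an interim superiority look at 0.0054 (overall error about 5.2%), and one sentence lets IQ share the primary question; both need a short correction

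*Protocol article*

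**What the plan says.** **Interim look.** Sample size calculation (Protocol article) provides for one O'Brien-Fleming interim analysis, which "is planned after half of the planned number of patients has reached their endpoints". Safety monitoring describes an interim analysis by the monitoring board "to investigate superiority of one of the treatment arms with regard to the primary outcome measure" and adds that a result with a two-sided p below 0.0054 "will be declared significant". The same paragraph gives a second condition: "If the difference in attention between groups is more than 1 SD", the board may advise early stopping.

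**Final test.** Outcome parameters gives one significance rule for all analyses: 95% "confidence intervals for group differences do not include 0", which it equates with a two-sided p below 0.05. Sample size calculation also uses two-sided alpha 0.05. No reduced final level is stated.

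**Primary question.** Outcome parameters states: "EpiTrack and IQ differences will be assessed cross-sectionally to answer the primary research question". Study objectives confines the primary objective to attention and executive function and lists IQ among the secondary objectives. Study design makes EpiTrack Junior at 1 year the primary outcome and says of IQ: "As secondary cognitive outcome measure, intelligence will be tested". Sample size calculation powers the trial on EpiTrack Junior alone.

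**The concern.** Two points bear on the rule by which the trial declares success.

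First, an interim look that can declare superiority uses part of the type I error. O'Brien-Fleming designs allow for this by lowering the final level slightly below 0.05. The article states an interim threshold and a final threshold, and the two do not fit the method it names. As written, the two-sided error on the primary endpoint is not the stated 5%, and the final 95% confidence interval does not match the design.

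Second, if two measures answer the primary question and no order or split of alpha is given, a positive IQ result beside a null EpiTrack result could be presented as a positive answer. The rest of the article does not intend this.

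**Working it through.** **Inputs from the Protocol article.** Difference 2.16 points, SD 4.70, 75 per arm, two-sided alpha 0.05, power 0.80, and one interim at half the patients (Sample size calculation). Interim level 0.0054 (Safety monitoring). Final level 0.05 (Outcome parameters).

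**1. The article's own sample size.** Normal approximation: n per arm = 2 × (1.960 + 0.842)² × 4.70² / 2.16² = 74.3, rounded up to 75. This reproduces the stated figure. Power at 75 per arm is 80.4% by the normal approximation and 79.8% by the noncentral t. Both use the full 0.05 at a single look.

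**2. Overall error of the stated pair.** Under the null hypothesis the interim and final statistics Z1 and Z2 are bivariate normal with correlation √f, where f is the information fraction. Overall error = 1 − P(|Z1| < 2.782 and |Z2| < 1.960), with 2.782 matching p = 0.0054 and 1.960 matching p = 0.05.

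| Information fraction f | Overall two-sided error | Final level that gives 0.05 overall |
|---|---|---|
| 0.3 | 0.0534 | 0.0465 |
| 0.5 | 0.0521 | 0.0479 (z = 1.979) |
| 0.6 | 0.0514 | 0.0485 |
| 0.7 | 0.0508 | 0.0492 |

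The fraction matters because Safety monitoring places the interim at 24 months, whereas Sample size calculation places it at half the patients. The two need not coincide.

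**3. The method named.** For two equally spaced looks the exact O'Brien-Fleming constants are z = 2.797 and 1.977, or p = 0.0052 and 0.0480. The stated 0.0054 is close to the first. The stated 0.05 is not the second.

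**4. Power after correction, 75 per arm.** With a final level of 0.0479, single-look power falls from 79.8% to 79.3% (noncentral t), or from 80.4% to 79.8% (normal). Two-look power, which counts the chance of crossing at the interim, is 80.0% (normal), so the sample size can stay.

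**5. The 1 SD condition.** With 37.5 patients per arm at the interim, the standard error of the difference in SD units is √(2/37.5) = 0.231. A 1 SD difference is therefore z = 1/0.231 = 4.33, p about 0.000015. If declaring superiority at the interim also required this difference, overall error with a final 0.05 would be 0.0500006, which is no inflation of any consequence.

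**6. IQ as a second test.** The article gives no correlation between EpiTrack and IQ, so these values are assumed. Suppose a significant result at 0.05 on either test counted as success. Independent tests give 1 − 0.95² = 0.0975. With correlation, ignoring the interim, the rate is about 0.095 at 0.3, 0.091 at 0.5, 0.084 at 0.7 and 0.070 at 0.9. The interim adds about 0.002 to each. If IQ is secondary, none of this applies and only step 2 remains.

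**The case against.** - **The method is named, so the final level is implied.** A two-look O'Brien-Fleming design carries a final level near 0.048, the 95% interval may be only a general convention, and a journal article may leave the exact boundary to the full protocol. This has weight as to intent. But the article does state a final threshold, makes no exception for the primary test, and uses 0.05 in the sample size. What is raised is a mismatch between stated figures, not an omission.
- **The excess is trivial.** It is about 0.2 percentage points at half information and less if the look is later. This stands and limits the severity.
- **The 1 SD condition may remove the excess.** It would if it were required in addition to p < 0.0054. The text does not say so: it is a ground on which the board may advise stopping, it is described in terms of reaction time, and p < 0.0054 is declared significant in a separate sentence.
- **The IQ sentence may only contrast cross-sectional with longitudinal analysis.** That reading is plausible, since the next sentence turns to change over time. The wording still conflicts with Study objectives, Study design and Sample size calculation.

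A reader might infer that the trial's false-positive rate is really 8 to 10%. The article does not support this. It nowhere says that significance on either EpiTrack or IQ is enough, and the correlations behind such figures are assumptions.

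**Conclusion.** Both points hold, at modest size. The stated interim and final levels give an overall two-sided type I error of about 5.2% on the primary EpiTrack test, not 5%. This assumes a look at half information and an interim p < 0.0054 that suffices to declare superiority. It is 5.34% at fraction 0.3 and 5.08% at 0.7.

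The IQ sentence is an internal contradiction about what answers the primary question. It would raise the false-positive rate to about 7 to 10% (assumed correlations 0.9 down to 0) only under an either-test rule that is not in the article. Severity is minor to moderate: neither point threatens the design or the sample size, but both concern the success criterion and should be settled before data accrue. Trial status records that no patients have yet been included.

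**What to change.** 1. In Outcome parameters, except the final primary EpiTrack test from the general 0.05 rule. State a two-sided level of about 0.0479 with a matching confidence interval of about 95.2% (100 × (1 − 0.0479) = 95.21), paired with the interim 0.0054. Alternatively, use the exact O'Brien-Fleming pair 0.0052 and 0.0480. Say that the final level will be recomputed by alpha spending if the look is not at half information.
2. In the sentence on the primary research question, delete the reference to IQ, so that only EpiTrack Junior at 12 months answers it. IQ remains secondary.
3. When making change 1, say in Safety monitoring whether the 1 SD difference is required in addition to p < 0.0054 or is a separate ground for advice, because the error calculation depends on it.

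**Cost:** a few sentences and about half a percentage point of single-look power at 75 per arm (79.8% to 79.3%), with no change in sample size.
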